### 2.13. Statistical Analysis

Data will be analyzed with SPSS (SPSS Inc., Chicago, IL, USA). The statistical analysis will allow us to determine the effects of the three different training programs on the cognitive, motor, and physical variables. The analysis will include subjects who completed all the pre- and post-tests. Data of the pre-test and post-test will be presented using descriptive statistics: mean, standard deviation, and percentage to describe the participants’ characteristics and performance on assessments. Comparisons within and between groups at baseline and post-intervention will be done using repeated measures ANOVA, and Newman-Keuls tests as post hoc analyses. The global Anova carried out between groups will allow testing the existence of a training effect (pre/post) for the different groups. Training is expected to improve performance for the three groups for both cognitive and physical variables.

With respect to the post-comparisons, we predict that no statistical differences should be observed between groups in the pre-test, while differences should be observed in the post-test. Specifically, post-hoc comparisons of the performance in the post-test should allow determining whether, as predicted, CT-fit training leads to greater benefits than the two other training modalities.

Baseline differences between groups will be carried out by observing the % of progress (pre/post-training) in each group, in some relevant measures. Adherence to programs will be measured by the absence rate (in %).

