### 2.4. Randomization

A computer-generated, random sequence of permuted blocks (block size = 3), will be created in order to assign the requested number (15) of screened participants to each group.

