### 2.12. Sample Size

The sample size calculation was performed using G. Power 3.1.9.7 (Kiel, Germany) [59]. In order to detect relevant between groups differences and in the changes from pre- to post-intervention, we calculated a sample size sufficient to detect medium effect sizes. Therefore, f = 0.25, α = 0.05, *p* = 0.80, were chosen to favor clinically significant effect sizes. To test the main hypotheses of the present study, 42 participants, are required. In order to compensate for possible dropouts, 3 more participants will be included. The three groups are composed of 15 participants each.

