
### 3.2. Strength and Weakness of the Present Study

Several important theoretical and practical issues are addressed in the present study. The first one lies in the comparison between circuit training protocols based on the association of aerobic exercise, muscular resistance training, and either TwM or MwT situations (i.e., CT-c and CT-fit, respectively). If our hypotheses are confirmed, this study will be the first one to show that MwT circuit training implemented via fitness gaming technologies are more effective multi-domain training protocols in older adults. The effects of the NW training protocol are also of great practical interest. Indeed, the results of our previous study [27] suggested that NW is a cheap and very effective way to improve physical, motor, and cognitive capacities in older adults. Notably, the sanitary situation (i.e., Covid-19) could make it difficult to regroup people over 65 years in closed spaces and then, to carry out the study. Additionally, some participants might be discouraged by the use of new technology in the CT-Fit protocol. However, nowadays they are becoming way more familiar with them. Thus, we do not anticipate that the use of technology will be a problem. On the contrary, it could be a motivating factor. Thus, the superiority of the CT-fit training over the more classical training conditions would allow us to conclude that this type of technology augmented training is among the most effective training to improve cognition and physical functions. These types of exercises would therefore be recommended as an optimal solution for the prevention of older adults’ cognitive and physical decline.

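### The completers-only analysis set selects on an event after randomisation, may discard observed outcomes, and rests on a dropout allowance of 3 with no stated loss rate

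*Protocol article*

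**What the plan says.** The trial randomises 45 people to three programmes, 15 per arm. Section 2.4 of the protocol article reads: "A computer-generated, random sequence of permuted blocks (block size = 3), will be created".

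Section 2.13 fixes the analysis set: "The analysis will include subjects who completed all the pre- and post-tests". The method is "repeated measures ANOVA, and Newman-Keuls tests as post hoc analyses". The article gives no analysis of all randomised participants, no outcome-by-outcome rule and no sensitivity analysis.

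Section 2.12 takes "f = 0.25, α = 0.05" and a power of 0.80, and concludes: "To test the main hypotheses of the present study, 42 participants, are required". It then adds: "In order to compensate for possible dropouts, 3 more participants will be included". No loss rate is given to support the 3.

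Section 3.2 says that "some participants might be discouraged by the use of new technology in the CT-Fit protocol". It goes on to say that the authors do not anticipate a problem and that the technology could motivate. The same section names Covid-19 as a difficulty for bringing people over 65 together indoors.

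**The concern.** Whether someone completes the post-tests is known only after allocation. Random allocation makes the arms comparable in expectation, but it does not do so for the subset who complete. If completion depends on the programme or on how a participant is doing, the completers in the three arms may differ for reasons other than the training. Every between-arm comparison in the trial uses this set, including the comparison of CT-fit with the other two arms.

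The wording raises a second problem. It asks for all tests, not for both values of the outcome being analysed. Taken literally, a participant with one missing result is dropped from outcomes that were fully observed. In a trial of 45, that is an avoidable loss.

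The third problem is that the sample size leaves room for only three such exclusions, and nothing in the article shows that three is enough.

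**Working it through.** **Inputs.** From Section 2.12: f = 0.25, α = 0.05, power 0.80, 42 required, 45 enrolled. From Section 2.13: three groups, two time points, repeated measures ANOVA. From the Abstract: 16 tests (7 cognitive, 6 motor, 3 physical). Not in the article, so assumed: the pre-post correlation ρ (0.5, range 0.3 to 0.7), the overall loss rate d, and the miss rate per test q.

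**Step 1: reproduce the 42.** For the group-by-time interaction, with k = 3 groups and m = 2 times, λ = f²·N·m/(1 − ρ), df1 = (k − 1)(m − 1) and df2 = (N − k)(m − 1).

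- N = 42: λ = 0.0625 × 42 × 2 / 0.5 = 10.5, df 2 and 39, power 0.803.
- N = 39: λ = 9.75, df 2 and 36, power 0.769.

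So 42 is the smallest total with equal arms that reaches 0.80, and the stated figure reproduces. It depends on ρ: at 0.3 the requirement is 60, at 0.7 it is 27.

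**Step 2: the allowance.** 45 − 42 = 3, 3/45 = 6.7%, one per arm (15 against 14). The fourth exclusion leaves 41.

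**Step 3: chance of keeping 42.** With independent losses at overall rate d, the number lost is binomial (45, d), and the requirement is at most 3 lost. The last column is 42/(1 − d) rounded up, with the next multiple of 3 in brackets where it differs.

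| Assumed loss d | Expected complete | P(at least 42) | Enrolment to keep 42 |
|---|---|---|---|
| 5% | 42.75 | 0.81 | 45 |
| 10% | 40.5 | 0.33 | 47 (48) |
| 15% | 38.25 | 0.08 | 50 (51) |
| 20% | 36 | 0.01 | 53 (54) |

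**Step 4: cost in power.** By number of complete cases, at ρ = 0.5: 45 gives 0.834, 42 gives 0.803, 41 gives 0.792, 39 gives 0.769, 36 gives 0.729. The loss is about one percentage point per participant.

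**Step 5: the literal reading.** If every test must be present and misses are independent at rate q, the expected number excluded is 45 × [1 − (1 − q)^T], where T is the number of results needed.

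| q | 16 post-tests only | 16 tests at both visits |
|---|---|---|
| 0.5% | 3.5 | 6.7 |
| 1% | 6.7 | 12.4 |

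Independence is the unfavourable assumption. If post-test misses clustered completely, so that a person missed the whole battery or none of it, a 0.5% rate would exclude only 45 × 0.005 ≈ 0.2 people. The count of 16 is also generous: under Section 2.9.6 the dual-task assessment includes the Oral Trail Making Test and uses the single-task gait trials. With 14 tests, the 0.5% figures become 3.0 and 5.9.

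**Step 6: where a single result could be missing.** The Timed-Stands outcome (Section 2.10.1) is the time for 10 repetitions, so someone who cannot finish them has no time to record. Under the literal rule, that person's valid Stroop and Trail Making results would be dropped too.

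**The case against.** The other side has a good deal to say, and much of it stands.

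- **Many tests score poor performance instead of losing it.** A reader might think that an unfinished shuttle walk costs a participant their place. Section 2.10.2 does not support that: stopping is the normal endpoint and the last completed level is the result. Unipedal balance is timed until balance is lost, and a failed stepping trial is repeated. Isolated missing tests may therefore be uncommon.
- **Section 3.2 has to be read to its end.** A reader might infer that CT-fit completers are known to differ from the other arms, or that the bias would favour CT-fit. The article raises discouragement as a possibility and then discounts it. It does not say that less able participants would be the ones to leave. Both non-comparability and its direction are possible, but neither is shown.
- **The allowance might be enough.** A reader might infer that the 3 would be used up almost at once. No loss rate is given, and at 5% overall loss the plan keeps 42 or more with probability 0.81. Falling short would also not cause a sudden collapse in power.
- **The sentence may mean less than it says.** It could mean only that both visits are needed for the outcome in hand, as repeated measures ANOVA requires. Losses would then be smaller.
- **Pre-tests may precede randomisation.** The article's text does not settle the order and the flow chart is not shown. If they do, a missing pre-test is not an exclusion after randomisation, and the post-test-only column is the relevant one.

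None of this removes the core. On either reading the set is defined by completing the post-tests, and the authors' expectation of good retention is no safeguard if it proves wrong.

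**Conclusion.** The point holds in a limited form. The article itself fixes a completers-only set, so this is not a detail left to an analysis plan. The rule selects on an event after randomisation and, read literally, discards observed outcomes. How much bias would follow, and in which direction, cannot be derived from the article.

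The certain part of the arithmetic is that the allowance is 3 of 45 and a fourth exclusion goes below 42. Whether that happens depends on assumed rates: unlikely at 5% overall loss, likely at 10% and very likely at 15%. The power figures assume ρ = 0.5, which reproduces the plan's 42 but is not stated. The per-test figures (3.5 or 6.7 excluded at a 0.5% miss rate) also assume independent misses, and clustering would lower them. The stronger grounds for change are the possible bias and the discarded data. The loss of power is secondary.

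**What to change.** Replace the sentence in Section 2.13 with wording such as:

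> Participants are analysed in the arm assigned, separately for each outcome, using all observed pre- and post-test values in a mixed model. Participants who stop training are still invited to the planned post-test. Analysis of those with all tests complete is a sensitivity analysis.

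Report the numbers randomised and analysed for each arm and outcome. In Section 2.12, state the loss rate that the 3 extra participants are meant to cover. If the sponsor keeps a completers set in any role, the text should say whether it means every test or both visits for the outcome concerned.

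An ANCOVA on available post-tests would not by itself meet this wording, because it leaves out anyone without a post-test. A mixed model does not fully solve that either: with two time points, a participant with no post-test adds little about change. The practical gain comes from keeping partly complete batteries and from seeking post-tests from those who stop training.

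The cost is small: a change of analysis wording, feasible in the planned SPSS, and a post-test invitation to those who stop. No new visits or tests are needed. N will vary slightly from one outcome to another.

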
### Aims and Hypotheses

The present experiment aims at comparing the effects on cognitive and motor functions of three types of training programs (NW, CT-c, and CT-fit), which differ in the nature of cognitive-motor exercises. It is hypothesized that, while all training would induce similar physical and motor fitness benefits, the CTs protocols would induce higher cognitive benefits than NW. Moreover, CT-fit should induce higher executive benefits than the two other training programs, thanks to the inclusion of cognitive stimulation through MwT conditions.

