### 2.8. Cognitive Assessment

Global cognitive status will be evaluated through the Montreal Cognitive Assessment (MoCA). This test is composed of different subparts and it is highly sensitive to detect MCI. Alternate versions of this test will be randomly assigned ipre- and post-test to each participant, in order to avoid test-retest effects [47]. Executive functions will be assessed through three different tests directed to: inhibition, switching, and working memory respectively. Inhibition processes will be tested with the Stroop test. Participants are seated in front of a computer and requested to indicate the color of the word appearing on the screen by pressing as quickly as possible on the corresponding key of the keyboard while inhibiting the word’s semantic. Four different colors can be presented: green, blue, red, and yellow. Thus, depending on the consistency between the semantic and the color, the condition is considered either congruent (C, e.g., the word “green” written in green) or incongruent (I, e.g., the word “green” written in red). In other trials, “neutral” words (N) are presented (N, e.g., arm, leg...), which are written in one of the different colors. After familiarization with 9 random words, 75 words will be presented for the test. Response times, that is, the time elapsing between the appearance of the word on the screen and manual pressing of the key on the keyboard, will be recorded. Each word remains present on the screen until the response is given. The mean response times (RT, in milliseconds) of the three different conditions will be calculated and compared between the others. Values above the ± 2SD of mean RT will be considered as outliers and excluded. *Switching capacities* will be evaluated through the Trail Making Test (TMT), which is composed of two parts, A and B, respectively. Part A requires participants to draw lines sequentially to connect 25 encircled numbers distributed on a sheet of paper. Part B requires participants to connect alternate numbers and letters (e.g., 1, A, 2, B, 3, C, etc.) with respect to the chronological and alphabetic order [48]. Total execution time (in milliseconds) and the number of errors will be recorded. Switching capacities are quantified by the ratio of the scores obtained in part-B divided by the scores obtained in part-A. Working memory will be assessed with a computerized test developed by the company HappyNeuron™ (Lyon, France), which is composed of two sequential parts. At first, a list of numbers will be provided to the participants via audio-speakers, and subsequently, a list of syllables. Once the full list is played, the participants are asked to repeat the last three items listened. Participants are informed that they cannot ask to listen to the track several times. The test starts with a familiarization trial. The examiner registers the correct answer and goes on with the trials. The time of completion (in seconds) and the total number of points will be recorded. Visuospatial capacities will be tested using the Rey Complex Figure copy task [49]. A complex figure comprising 18 graphic elements, a blank sheet (to copy), and a stopwatch are needed to run the test. The figure is placed in front of the participant, who must reproduce it to the best of his or her ability. The figure is exposed to the subject for a minimum of two and a half minutes and a maximum of five minutes, although it is not removed if the subject exceeds this time. The participant is allowed to copy the figure with a pen, and he/she can self-correct if he/she wants to. After the participant finishes their copy, the figure is removed. The total time required to copy the figure is measured in seconds and the quality of the response is measured for each of the 18 elements that make up the figure. A score between 0 and 2 points is given for each of these elements (maximum score of 36), depending on their accuracy, possible distortion, and location.

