### 3.1. Differences in the Effectiveness of the Three Training Protocols on Cognitive, Physical, and Motor Capacities

In accordance with the literature [60,61], global cognitive performance is expected to be enhanced after training in all three groups. However, it is expected that the CT-c and CT-fit protocols will lead to larger improvements in EF than NW. This should result from the combination of the effects of coordination training and aerobic exercise on cognition [10,15] that is allowed by the synergy between facilitation and guidance effects that occur at the brain level [35,62,63]. Moreover, a strong hypothesis is that CT-fit will be a more effective training protocol to improve EFs [64]. It should be the case since the MwT training conditions used in the CT-fit require the implementation of cognition in action, which is closer to real-life situations than TwM task conditions used in the CT-c. Additionally, according to Herold and colleagues [30], MwT training has a higher potential than TwM training to stimulate brain plasticity, due to the multiple sensory systems activated and involved [30]. In summary, one could expect that the CT-fit will show larger benefits for executive function as compared to the other groups. Nevertheless, the two other forms of training are also predicted to lead to improvements in EFs. In addition, due to the presence of specific DT exercises in the CT-c, participants in this training protocol will show better dual-task performance in the related tests. The question remains, however, of the possible benefits of the other protocols on DT performance. This issue will be addressed. Finally, visuospatial capacities are expected to be more improved by the CTs, especially by the CT-fit due to the embodied characteristics, than in NW. Indeed, it has been previously demonstrated that coordination training specifically impacts visuospatial capacities [12,14]. With respect to physical fitness, reflected by cardiovascular capacities, in accordance with [name] and colleagues’ [27] study, it is expected that all three groups will improve their cardiovascular capacities. This could occur if the mean level of effort, indexed by mean heart rate calculated during the different sessions for the three training programs, is roughly equivalent [27]. If not the case, a difference could be observed between the three groups in the relative test. In case of differences between the three groups, we will analyze heart rate and data from the Borg scale to determine whether one of three training protocols was (at least perceived) of higher intensity, relative to the others. Regarding muscular capacities, it is expected that the two CTs will show a significant improvement in the related tests, larger than those observed in NW. Motor fitness is expected to be impacted by the three training programs, as previously observed by [name] and collaborators [27]. However, one expects that the two CTs should be more effective than NW in this respect. Indeed, presumably, NW requires the repetition of automated arm-leg coordination (stabilization by quantitative repetition), while the CT programs allow developing whole-body and multi-limb coordination through a variety of different exercises, which may be learned over the different sessions and could allow qualitative incorporation of new behavioral patterns in the repertoire of existing ones. Thus, NW and CTs are hypothesized to develop motor fitness and coordination capacities [27], while differently, due to the respective part of repetitive practice of automated movements, variety and novelty of the to be learned coordinated movements. In addition, one expects to observe an improvement in walking speed (cm/sec), in the single task in the NW group relative to the CT groups. Additionally, a decrease in the size of the base of support (cm) is expected more for the CTs groups, proving the effectiveness of the specific balance training proposed in these training groups. Finally, as in our previous study, the percentage of responders (i.e., participants who progressed in the exercise under interest) will be also assessed to check whether it is higher for some protocols, though differentially for specific tests. In the lack of related studies available in the literature, no hypothesis is made in this respect but these analyses could help to interpret eventual differences of performance between groups and tests.

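### The CT-fit hypothesis is stated, but no outcome decides it: several unranked cognitive tests share one procedure with no stated control across them, and the muscular and motor predictions conflict

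*Protocol article*

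**What the plan says.** The Aims and Hypotheses section states that "CT-fit should induce higher executive benefits than the two other training programs". Section 2.13 repeats the comparison of CT-fit with the two other programs as the purpose of the post hoc tests at post-test, this time without a domain. The contrast of interest is therefore on record.

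Section 2.8 spreads the domain over several tests: "Executive functions will be assessed through three different tests directed to: inhibition, switching, and working memory respectively". None is placed first. The Abstract lists seven cognitive tests: MoCA, Trail Making, Stroop, working memory, Rey figure copy, oral Trail Making and dual-task. Most give more than one score. Section 2.13 applies one method to the cognitive, motor and physical variables alike: "Comparisons within and between groups at baseline and post-intervention will be done using repeated measures ANOVA, and Newman-Keuls tests as post hoc analyses".

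Section 2.12 gives the design values, "f = 0.25, α = 0.05, *p* = 0.80, were chosen to favor clinically significant effect sizes", and concludes: "To test the main hypotheses of the present study, 42 participants, are required". It ties neither the effect size nor the main hypotheses to an outcome.

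On physical and motor fitness, the Aims predict that "all training would induce similar physical and motor fitness benefits". Section 3.1 says of motor fitness that "one expects that the two CTs should be more effective than NW in this respect", and expects larger muscular gains in the circuit arms than in NW. It also expects single-task walking speed to favour NW.

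**The concern.** Newman-Keuls acts on the three group means within one outcome. It does nothing about the number of outcomes. If each test is judged at 0.05, as the single alpha in section 2.12 suggests, the overall false-positive rate grows with the number of scores. Nothing says whether one, two or all three executive tests must favour CT-fit for the hypothesis to count as supported.

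The intended conclusion is strong. Section 3.2 says that superiority of CT-fit would make this type of exercise a recommended solution for preventing decline. Such a statement should rest on a result identified in advance.

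The second problem concerns interpretation. Where one section predicts no difference and another predicts a difference on the same tests, no result can count against the hypotheses.

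**Working it through.** **Step 1: reproduce the sample size.** From section 2.12: f = 0.25, alpha = 0.05, power = 0.80, three groups. From section 2.1: two measurements. The pre-post correlation is not stated; 0.5 is assumed. For the group-by-time interaction, the noncentrality is f² × N × m / (1 − rho).

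- N = 42: 0.0625 × 42 × 2 / 0.5 = 10.5, with df 2 and 39 and critical F 3.24. Power is 0.803.
- N = 39: power is 0.769, so 42 is the smallest balanced total.
- Other correlations give N = 81 (rho 0), 60 (0.3) or 27 (0.7). At rho 0.5, a between-group main effect would need 120 and a pure time effect 36.

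So 42 matches one interaction test on one outcome at 0.05.

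**Step 2: error rate over several outcomes, independent case.** The chance of at least one false positive is 1 − 0.95^k:

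- k = 3 (executive tests): 14.3%
- k = 7 (cognitive tests): 30.2%
- k = 17 (scores): 58.2%

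The 17 is an approximate count from sections 2.8 and 2.9.6, and other counts are possible: MoCA 1, Stroop response times 3, Trail Making 4 (two times, errors, B/A ratio), working memory 2, Rey 2, oral and dual-task indices 5.

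**Step 3: simulate the planned procedure.** Change scores were simulated with no true differences, 14 completers per arm, equally correlated normal outcomes and Newman-Keuls at 0.05 within each outcome (df 39), with 40,000 runs per row. Critical studentised ranges are 3.45 for three means and 2.86 for two.

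| Outcomes | Correlation between outcomes | Any group difference | CT-fit over at least one comparator | CT-fit over both, same outcome |
|---|---|---|---|---|
| 3 | 0 | 14% | 6% | 1% |
| 3 | 0.5 | 13% | 5% | 1% |
| 7 | 0 | 30% | 13% | 3% |
| 7 | 0.3 | 28% | 12% | 2–3% |
| 7 | 0.5 | 24% | 10% | 2% |
| 17 | 0 | 58% | 30% | 6% |
| 17 | 0.5 | 40% | 18% | 4% |

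**Step 4: power if several tests stay co-equal.** Using the step 1 formula with a Bonferroni alpha:

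- Three tests (0.05/3 = 0.0167): power at N = 42 is 0.65, and 57 completers are needed for 0.80.
- Seven tests (0.05/7 = 0.0071): power at N = 42 is 0.52, and 66 completers are needed.

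**Step 5: compare the predictions.**

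| Domain | Aims | Section 3.1 |
|---|---|---|
| Muscular (under physical fitness in 2.10) | Similar in all groups | Circuit arms gain more than NW |
| Motor fitness | Similar in all groups | Circuit arms gain more than NW; walking speed favours NW |
| Cardiovascular | Similar in all groups | All groups improve |

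The first two rows conflict. The third does not.

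**The case against.** The strongest reply is that the plan is less open than it looks. It names the contrast, names the domain, and assigns that domain to three tests. Within each outcome Newman-Keuls controls the error over the three group comparisons when all groups are equal. On the three executive tests, CT-fit falsely beats some comparator only 5 to 6% of the time, and beats both, which is what the hypothesis predicts, about 1% of the time. Some of the seven cognitive tests also carry other predictions: CT-c is expected to do better on dual-task. All of this stands.

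A reader might therefore go too far in four ways.

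- **That no contrast is specified.** One is. It lacks a deciding outcome and a rank among the other predictions.
- **That a chance confirmation of CT-fit is likely.** Unadjusted pairwise t tests over seven scores would give a CT-fit difference in either direction in 38 to 48% of trials. That is not the planned procedure; step 3 gives the rates that apply.
- **That all physical predictions conflict.** The cardiovascular ones agree.
- **That the authors will take non-significance as proof of similarity.** No section says so. The documents support only a caution.

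It is also fair that detailed multiplicity rules often sit in a full protocol or analysis plan that is not shown. Their absence here is not the point. This article fixes a sample size tied to no outcome and publishes two incompatible sets of hypotheses. A separate analysis plan would not by itself make the Aims and section 3.1 agree.

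**Conclusion.** The point holds in a limited form. The contrast is named, but no outcome decides it. A trial sized as for one test at 0.05 spreads its claim over three executive tests, or seven cognitive tests on the broader reading. The chance of some false group difference is then about 13 to 14% or 24 to 30% rather than 5%, and about 40 to 58% if some 17 scores are all examined. False findings specific to CT-fit are rarer: over the seven, 10 to 13% against at least one comparator and 2 to 3% against both on the same test.

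These figures assume no true differences, 14 completers per arm, normal outcomes with equal correlation between 0 and 0.5, and 0.05 per outcome. That last level is inferred from section 2.12; section 2.13 does not state it. The match to N = 42 assumes a pre-post correlation of 0.5.

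The contradiction between the Aims and section 3.1 on muscular and motor fitness needs no assumption.

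**What to change.** Before any data are seen:

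1. Name one primary executive outcome. A composite of the three tests in section 2.8 is one reasonable choice, with the score from each test, its direction and its standardisation defined. A single test would also serve.
2. Name one deciding test: the group-by-time interaction on that outcome at 0.05, followed by ranked contrasts of CT-fit versus CT-c and CT-fit versus NW. Putting CT-c first has the advantage that, by section 2.6, the same coach runs both circuit arms.
3. Tie the sample size to that outcome and state the assumed pre-post correlation. With one outcome, 42 stands under the assumption above. The 0.803 is power for the overall interaction, not for each contrast.
4. Label all other outcomes secondary or exploratory.
5. Make the Aims and section 3.1 agree on muscular and motor fitness. Do not read non-significance as similarity; if similarity is to be claimed, say in advance what would show it.

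The Data Availability statement says that data have not yet been collected, so this costs only wording. The price is that findings on single tests lose confirmatory status, and a composite may dilute an effect confined to one executive component. Keeping the three tests co-equal with Bonferroni would instead need 57 completers.
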